Rybniker et al1 recently used an intracellular assay procedure to screen for drugs with antituberculous potential. They found that lansoprazole was highly active against TB in cell culture, when transformed intracellularly from the prodrug lansoprazole to lansoprazole sufoxide. Strong activity was also found against drug-resistant TB clinical isolates suggesting further clinical investigation is warranted. Of note, other PPIs (omeprazole and pantoprazole) were not found to have anti-tuberculous activity. To date there have been no clinical studies assessing whether lansoprazole as used in routine clinical care has such anti-tuberculous properties. Given the widespread use of PPIs over many years, we believe the CPRD provides an ideal opportunity to investigate whether lansoprazole may be associated with a lower risk of TB disease by making a direct comparison between lansoprazole users and users of omeprazole or pantoprazole.

1. **Study Type**

This is a hypothesis testing study

1. **Study Design**

This will be a cohort study comparing the rate of TB disease in people treated with lansoprazole, compared with people treated with omeprazole or pantoprazole. This design will minimise confounding because both lansoprazole exposed and unexposed patients will be receiving a PPI and will therefore have similar underlying health problems which may be associated with the risk of TB disease.

1. **Sample Size**

A feasibility count from Jan 2015 CPRD GOLD indicates the following:

- Lansoprazole new users n=744,144
- Omeprazole and pantoprazole new users n=1,182,888
- Lansoprazole new users with subsequent TB n=1,227

At this stage we cannot be sure how many incident TB cases will occur during PPI exposure, rather than after exposure has ended. Nor can we state with confidence what effect size we expect to detect. Table 1 therefore gives estimates of power under a range of assumptions, based on a conservative 1:1 comparison between lansoprazole and omeprazole or pantoprazole.

|  | *Number of exposed cases* | | | |
| --- | --- | --- | --- | --- |
| *Relative Risk* | **1,200** | **800** | **500** | **200** |
| **0.9** | 0.73 | 0.56 | 0.38 | 0.18 |
| **0.8** | >0.99 | >0.99 | 0.94 | 0.61 |
| **0.7** | >0.99 | >0.99 | >0.99 | >0.99 |
| **0.6** | >0.99 | >0.99 | >0.99 | >0.99 |
| **0.5** | >0.99 | >0.99 | >0.99 | >0.99 |

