Table 1: Estimates of power to detect a range of possible relative risks, under a range of assumptions about the number of likely lansoprazole exposed TB cases

For most of the assumptions tested, we will have adequate power to detect an association with lansoprazole assuming a protective association of 0.8 or greater, which we believe would represent a clinically relevant effect size.

1. **Data Linkage Required (if applicable)**

Patient-level index of multiple deprivation data are required to assess for confounding as it is likely that risk of TB will vary by socioeconomic status. Since this is only available for patients in the linkage scheme, we propose to use practice-level index of multiple deprivation for the remainder of patients (rescaled to be on the same scale as the patient level scores, using observations where both are available). We have used this strategy successfully in previous CPRD studies.

We will also use HES (in- and out-patient data) to identify cases of TB recorded in hospital.

1. **Study Population**

The source population for this study is all patients aged 16 years or over with acceptable user status registered in the entire CPRD, with up-to-standard (uts) follow up of at least 12 months.

From the source population we will select all patients who are:

1. New users of lansoprazole; defined as people starting treatment with lansoprazole after at least 12 months uts follow up, with no previous record of receiving a PPI.
2. New users of omeprazole or pantoprazole; defined as people starting treatment with omeprazole or pantoprazole after at least 12 months uts follow up, with no previous record of receiving a PPI.

Exposure to lansoprazole, omeprazole and pantoprazole will be defined by prescription records, as conducted previously by this research group2.

All patients with a record of TB disease prior to their first PPI will be excluded from the study.

1. **Selection of comparison group(s) or controls**

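### If 1:1 means equal exposure, Table 1's case counts do not fit its relative risks: six powers are 1 to 5 points too low, and the RR 0.7/200-case entry is too high

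*Protocol*

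**What the plan says.** The Sample Size section of the protocol lists feasibility counts of 744,144 lansoprazole new users and, for the comparator, "Omeprazole and pantoprazole new users n=1,182,888". It says that neither the number of TB cases during exposure nor the effect size is known in advance. It therefore tabulates power over a grid, "based on a conservative 1:1 comparison between lansoprazole and omeprazole or pantoprazole".

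The rows of Table 1 are relative risks from 0.9 to 0.5. The columns are 1,200, 800, 500 and 200 exposed cases, and the caption confirms that the grid runs "under a range of assumptions about the number of likely lansoprazole exposed TB cases". The entries that matter here are the RR 0.9 row, "0.9 | 0.73 | 0.56 | 0.38 | 0.18", the RR 0.8 row, "0.8 | >0.99 | >0.99 | 0.94 | 0.61", and the RR 0.7 row, "0.7 | >0.99 | >0.99 | >0.99 | >0.99".

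The text below the table concludes: "For most of the assumptions tested, we will have adequate power to detect an association with lansoprazole", for a relative risk of 0.8 or stronger. The section gives no alpha, sidedness, formula or comparator case count for the table, and does not say whether 1:1 refers to people, person-time or cases.

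**The concern.** A cell of Table 1 is defined by the exposed case count, the RR and the 1:1 ratio. If the ratio is one of exposure, these three fix the comparator case count. For example, 200 lansoprazole cases at RR 0.8 go with 200/0.8 = 250 comparator cases, or 450 events in all. The printed power of 0.61 corresponds to 400.

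The equal-exposure reading is the natural one. The feasibility counts beside the table are counts of users, and the Data/Statistical analysis section compares exposed time with exposed time.

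Table 1 is the only support the section offers for its statement about power, so its entries should follow from its labels. The amendments record that the study has since been run and an association found. What is at stake is therefore the accuracy of the record, not a design decision.

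**Working it through.** **Inputs.** Exposed cases n = 1,200, 800, 500, 200 and RR = 0.9 to 0.5 (Table 1); ratio 1:1 (Sample Size text). Two-sided alpha of 0.05 is assumed, in line with the 95% confidence intervals in the Data/Statistical analysis section. One-sided 5% does not reproduce the table (RR 0.9 with 1,200 cases would be 0.825, against 0.73 printed).

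**Formula.** Schoenfeld: power = Φ(√(D·p(1−p))·|ln RR| − 1.96), where D is total events and p the lansoprazole share of exposure.

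**Step 1: reproduce the printed figures.** Take D = 2n and p = 0.5. For RR 0.8 with 200 cases, D = 400, so √(400 × 0.25) × 0.2231 = 2.231 and power = Φ(0.271) = 0.607 (printed 0.61). This version reproduces 19 of the 20 cells, including all six printed below 0.99.

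**Step 2: make the counts consistent with the RR at 1:1 exposure.** Comparator cases = n/RR, so D = n(1 + 1/RR), with p = 0.5. For the same cell, D = 200 + 250 = 450, so √(450 × 0.25) × 0.2231 = 2.367 and power = Φ(0.407) = 0.658.

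| RR | Exposed cases | Printed | D = 2n | D = n(1 + 1/RR) |
|---|---|---|---|---|
| 0.9 | 1,200 | 0.73 | 0.733 | 0.755 |
| 0.9 | 800 | 0.56 | 0.559 | 0.581 |
| 0.9 | 500 | 0.38 | 0.384 | 0.402 |
| 0.9 | 200 | 0.18 | 0.182 | 0.190 |
| 0.8 | 500 | 0.94 | 0.942 | 0.963 |
| 0.8 | 200 | 0.61 | 0.607 | 0.658 |
| 0.7 | 200 | >0.99 | 0.946 | 0.976 |

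All other cells exceed 0.99 under both versions, as printed.

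**Step 3: check against other formulas.** A Wald test on the log rate ratio has standard error √(1/n + RR/n) when comparator cases are n/RR. It gives 0.653 for RR 0.8 with 200 cases and 0.754 for RR 0.9 with 1,200. A two-proportion calculation gives 0.655 and 0.755. Both stay within about 0.005 of Schoenfeld.

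**Step 4: the RR 0.7, 200-case cell.** With D = 400, √100 × 0.3567 = 3.567 and power = Φ(1.607) = 0.946. With RR-consistent counts it is 0.976 by Schoenfeld, 0.973 by two proportions and 0.972 by Wald. None of these 1:1 calculations reaches the printed >0.99.

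**Step 5: effect on the conclusion.** Of the 16 cells with RR 0.8 or stronger, only RR 0.8 with 200 cases is below 80%, both as printed (0.61) and as recomputed (0.658). In the RR 0.9 row no cell reaches 80% either way.

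**Step 6: the ratio in the user counts, for context only.** k = 1,182,888/744,144 = 1.59. With comparator cases = k·n/RR, RR 0.8 with 200 cases becomes 0.757 (Schoenfeld), 0.737 (two proportions) or 0.730 (Wald). RR 0.9 with 1,200 cases becomes 0.840, 0.834 or 0.831.

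**The case against.** The strongest reply is that the protocol never says the 1:1 ratio is one of exposure and prints no comparator case count, so the inconsistency appears only once the reader supplies that meaning. This stands as a limit: the finding is conditional on equal exposure. Reading 1:1 as equal cases is possible, but at RR 0.8 it would need comparator exposure of only 0.8 times lansoprazole exposure. That sits badly with a plan that includes every comparator new user and counts 1.59 of them per lansoprazole new user.

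It is also tempting to infer that the authors gave both groups the same number of cases. The match does not prove this. It fixes total events at 2n, not how they split. Wald power for 2n events divided RR:1 gives 0.731, 0.557, 0.383, 0.182, 0.939 and 0.602, nearly as close to the printed values. On that account the column heading is loose, because the lansoprazole cases would then be fewer than n.

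A reader might also take the gap to the 1.59:1 figures, 12 to 15 points for RR 0.8 with 200 cases, as a misstatement. It is not one. The protocol prints both user counts and openly chooses 1:1 as the conservative case. The larger figures also depend on the formula, and on on-drug time dividing as starters do, although patients may switch drugs or stop.

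Finally, shifts of up to 5 points are small beside a sixfold range of case counts, and most err on the cautious side. This is true and keeps the point minor, but it does not cover the RR 0.7/200 cell, which errs the other way.

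**Conclusion.** The point holds as a minor numerical correction. If 1:1 means equal exposure and the test is two-sided at 5%, six cells of Table 1 understate power by about 1 to 5 points, most at RR 0.8 with 200 cases (0.61 printed, about 0.65 to 0.66 recomputed). The RR 0.7 cell with 200 cases overstates power: >0.99 is printed, against 0.946 with the 2n events that reproduce every other cell, or 0.972 to 0.976 with RR-consistent counts. This cell is the clearest error, since neither reading of 1:1 yields it. The table therefore does not understate power throughout. No cell crosses 80% at 1:1, and the statement that power is adequate under most assumptions for RR 0.8 or stronger is unaffected.

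**What to change.** Recompute Table 1 with comparator cases equal to exposed cases divided by RR at 1:1, which also corrects the RR 0.7/200 cell. Add a line giving alpha, sidedness, the formula, and whether 1:1 refers to people, person-time or cases. If equal case counts or a 2n event total were intended, say so, relabel the columns to match, and still correct the RR 0.7/200 cell.

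A second version at 1.59:1 is optional. It should be labelled as assuming that on-drug time divides as starters do, and not presented as a correction.

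The cost is one recalculated table and one sentence of method. The sentence on adequate power can stay, and nothing changes in the data, the population or the analysis.

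### Table 1 prints power >0.99 for a relative risk of 0.7 with 200 exposed cases; the calculation that matches the other 19 cells gives 0.95

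*Protocol*

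**What the plan says.** The Sample Size section says that the number of TB cases arising during PPI exposure is not known, and that the effect size to expect cannot be stated with confidence. It therefore tabulates power over a grid, "based on a conservative 1:1 comparison between lansoprazole and omeprazole or pantoprazole". The columns are numbers of lansoprazole-exposed TB cases (1,200, 800, 500, 200). The rows are relative risks from 0.9 to 0.5. No formula, significance level or sidedness is given for the table.

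The rows are:

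- "0.9 | 0.73 | 0.56 | 0.38 | 0.18"
- "0.8 | >0.99 | >0.99 | 0.94 | 0.61"
- "0.7 | >0.99 | >0.99 | >0.99 | >0.99"
- "0.6 | >0.99 | >0.99 | >0.99 | >0.99"
- "0.5 | >0.99 | >0.99 | >0.99 | >0.99"

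Below the table the protocol concludes: "For most of the assumptions tested, we will have adequate power to detect an association with lansoprazole", on the assumption of a protective association of 0.8 or stronger, which it regards as clinically relevant.

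**The concern.** In the 200-case column the printed power goes from 0.61 at a relative risk of 0.8 to above 0.99 at 0.7. That step is too large. In any test based on the log relative risk with a fixed number of events, the expected test statistic scales roughly with |ln RR|. Moving from 0.8 to 0.7 multiplies it by 0.3567/0.2231 = 1.60. Power of 0.61 corresponds to an expected statistic of about 2.23, and 1.60 × 2.23 = 3.57 falls short of the 4.29 needed for power of 0.99.

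The table exists to show how power holds up if few TB cases fall in on-treatment time, and the 200-case column is its worst case. As printed, the row for 0.7 looks insensitive to the number of cases across the whole range, when power has in fact begun to drop.

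**Working it through.** **Inputs.** Relative risks, exposed-case counts and stated powers are from Table 1. The 1:1 basis is from the Sample Size text. Two-sided alpha 0.05 is an assumption; it agrees with the 95% confidence intervals planned in the Data/Statistical analysis section and is tested against the table below.

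**Formula.** Schoenfeld power for *D* total events under 1:1 is Φ(|ln RR| × √(D/4) − 1.96). With *n* exposed cases and D = 2n this becomes Φ(|ln RR| × √(n/2) − 1.96).

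**Step 1: reproduce the plan's own figures.**

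| RR | 1,200 | 800 | 500 | 200 |
| --- | --- | --- | --- | --- |
| 0.9 | 0.733 (stated 0.73) | 0.559 (0.56) | 0.384 (0.38) | 0.182 (0.18) |
| 0.8 | 0.9998 (>0.99) | 0.994 (>0.99) | 0.942 (0.94) | 0.607 (0.61) |
| 0.7 | 1.000 (>0.99) | 1.000 (>0.99) | 0.9999 (>0.99) | **0.946 (>0.99)** |
| 0.6 | 1.000 (>0.99) | 1.000 (>0.99) | 1.000 (>0.99) | 0.999 (>0.99) |
| 0.5 | 1.000 (>0.99) | 1.000 (>0.99) | 1.000 (>0.99) | 1.000 (>0.99) |

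Nineteen of the 20 cells agree at the printed precision. Six of these are numeric, from 0.18 to 0.94, and they identify the method. The other 13 print only >0.99 and are merely consistent with it.

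**Step 2: the disputed cell.** |ln 0.7| = 0.3567; √(200/2) = 10; product 3.567; minus 1.96 = 1.607; Φ(1.607) = 0.946. The gap to the stated figure is at least 0.990 − 0.946 = 0.044. Type II error is 1 − 0.946 = 0.054.

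**Step 3: exposed cases needed for 0.99 at RR 0.7.** n = 2 × [(1.960 + 2.326)/0.3567]² ≈ 289.

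**Step 4: other conventions for the same cell.**

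| Convention (200 exposed cases, RR 0.7) | Power |
| --- | --- |
| Schoenfeld, 200 taken as total events, two-sided | 0.713 |
| Wald on log rate ratio, 200 taken as comparator cases, two-sided | 0.899 |
| Freedman, 400 events, two-sided | 0.942 |
| Wald, comparator cases = 200/0.7, two-sided | 0.972 |
| Two proportions, 744,144 per arm, 200 exposed cases, two-sided | 0.973 |
| Schoenfeld, total events 200 × (1 + 1/0.7), two-sided | 0.976 |
| Same events, one-sided 0.05 (highest of the one-sided variants) | 0.989 |

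Under the stated 1:1 basis none exceeds 0.99. The conventions that come closest also miss the numeric cells. The two-sided variant giving 0.976 returns 0.755 where 0.73 is printed and 0.658 where 0.61 is printed. Its one-sided counterpart returns 0.843 for the 0.73.

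**The case against.** The strongest objection is that the formula and alpha are inferred, and that a reading exists which does reach the printed value. With the protocol's own new-user counts the comparator-to-lansoprazole ratio is 1,182,888/744,144 = 1.59. Then 200 exposed cases at RR 0.7 go with 200 × 1.59/0.7 ≈ 454 comparator cases, and two-sided Schoenfeld gives 0.993 (a Wald test gives 0.988). This is true, so it cannot be said that no calculation of any kind exceeds 0.99. But it departs from the 1:1 basis on which the table is said to rest, and it gives 0.84 where the table prints 0.73. It cannot be the source of the table.

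The objection is stronger on consequences, and most of that stands:

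- Power of 0.946 exceeds the usual 0.80 or 0.90 targets.
- The conclusion under the table is tied to a relative risk of 0.8 and remains true.
- The 200-case column already shows weak power where it matters most, at 0.18 and 0.61.
- At the actual ratio of users, power in this cell would be about 0.99.
- The cohort size is set by the database, and the Amendment section says that the study has been carried out as outlined. The correction alters neither design nor analysis.

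**Conclusion.** The entry is wrong as written. On the table's own 1:1 basis, power for a relative risk of 0.7 with 200 exposed cases is 0.946, or 0.95 to two decimals, not above 0.99. The type II error is about 5.4% rather than under 1%.

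This rests on two-sided alpha 0.05 and total events equal to twice the exposed cases. Neither is stated, but together they match all six numeric cells. The other two-sided 1:1 conventions tried run from 0.71 to 0.976 and the one-sided ones from 0.81 to 0.989, so the conclusion that the cell is overstated does not depend on the exact choice.

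The arithmetic is certain and the effect modest. The error corrects the record of planned power, in the table's least favourable column; the stated conclusion on adequacy of power is unaffected.

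**What to change.** In Table 1, replace >0.99 by 0.95 in the cell for a relative risk of 0.7 and 200 exposed cases. Add a line under the table giving the formula, the two-sided 5% level and the assumption that total events are twice the exposed cases, after confirming that these were the settings used. The sentence on adequate power can stay.

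The cost is one table cell and one line of text. The stated power becomes slightly less favourable in that cell and nothing else changes.

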CPRD linked Hospital Episodes Statistics (HES) in- and out-patient data will also be searched for codes indicating tuberculosis (A15-A19). A sensitivity analysis restricted to the CPRD HES-linked practices and time periods will be conducted, taking the earliest of CPRD or HES identified TB disease.

Covariates to be explored for their potential confounding nature will be age, sex, calendar year, smoking behaviour, body mass index, alcohol use, ethnicity, drug abuse, the use of inhaled/oral corticosteroids, travel vaccines, antimalarials, diabetes, rheumatoid arthritis, irritable bowel disease, chronic obstructive pulmonary disease, asthma, chronic kidney disease, depression, leukaemia, lymphoma, myeloma any record signifying the use of chemotherapy, a record of HIV infection and index of multiple deprivation score. Of note, ciclosporin and tacrolimus, both immunosuppressive drugs, are known to interact with omeprazole but not other PPIs. It is possible that people at higher risk of TB will therefore be given PPIs other than omeprazole and for this reason, patients with a history of use of either drug will be excluded from the study population.

1. **Data/ Statistical analysis**

Each participant’s follow up time will begin at the first prescription for lansoprazole or omeprazole/pantoprazole. All subsequent time will be classified as one of the following

- *Lansoprazole exposed* – all time covered by lansoprazole prescriptions, including a 60 day period after the estimated end of treatment date, to allow for stock piling and non-adherence
- *Omeprazole/pantoprazole exposed* – all time covered by omeprazole/pantoprazole prescriptions including a 60 day period after the estimated end of treatment date, to allow for stock piling and non-adherence. This will be the baseline against which other exposures are compared.
- *Unexposed* – all time between lansoprazole/omeprazole/pantoprazole exposure periods, or between the end of PPI exposure and the end of follow up. This time is being handled separately as it is plausible that a period of time off a PPI may be a marker of important changes in underlying health, with an associated change in the risk of TB disease

Where patients switch directly between one PPI and another, exposure will be updated to the new PPI from the date it is prescribed, assuming stock-piled drug is no longer taken.

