End of follow up will be defined as the earliest of first recorded TB disease, death, transfer away, end of UTS or last data collection date.

Examples of how patient follow up time will be allocated are shown in Figure 1.

*Figure 1: Example Patient Exposure Timelines*

1. Lansoprazole exposure only

12 months follow up with no PPI

End uts

Lansoprazole prescription

EXPOSURE GROUP

Lanoprazole

1. Omeprazole or pantoprazole only

12 months follow up with no PPI

End uts

Omeprazole prescription

EXPOSURE GROUP

Omeprazole

or pantoprazole

1. Lansoprazole and omeprazole/pantoprazole

12 months follow up with no PPI

End uts

Lansoprazole prescription

Omeprazole prescription

EXPOSURE GROUP

Lansoprazole

Omeprazole

or pantoprazole

4. Lansoprazole with Breaks

12 months follow up with no PPI

End uts

Lansoprazole prescription

EXPOSURE GROUP

Lansoprazole

Unexposed

5. Lansoprazole, omeprazole/pantoprazole and breaks

12 months follow up with no lansoprazole

End uts

Pantoprazole prescription

Lansoprazole prescription

EXPOSURE GROUP

Lansoprazole

Unexposed

Omeprazole

or pantoprazole

The primary comparison of interest is the risk of TB comparing lansoprazole exposed time with omeprazole or pantoprazole exposed time. People starting treatment with omeprazole or pantoprazole but later receiving lansoprazole will transition to the lansoprazole group at that time and vice versa. Follow up for each patient will end at the earliest of; TB disease, transfer out, death or end of uts follow up.

Descriptive analyses will be performed, comparing the distribution of the following variables between patients starting lansoprazole and those starting omeprazole/pantoprazole: Age, sex, calendar year, smoking behaviour, body mass index, alcohol use, ethnicity, drug abuse, the use of corticosteroids, any record signifying any prior use of chemotherapy, travel vaccines, antimalarials, diabetes , rheumatoid arthritis, irritable bowel disease, chronic obstructive pulmonary disease, asthma, chronic kidney disease, depression, leukaemia, lymphoma, myeloma, a record of HIV infection and index of multiple deprivation score.

Cox regression will be used to estimate hazard ratios and 95% confidence intervals, comparing lansoprazole exposed time against omeprazole or pantoprazole exposed time. A crude model will be constructed with just the main exposure variable, followed by a model adjusting for potential confounders.

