We will fit an interaction term to look for effect modification between lansoprazole exposure and age.

As a sensitivity analysis we will vary the time following the end of estimated treatment duration after which therapy cessation is assumed, from 60 to 90 days. A further sensitivity analysis will censor all patients after a cessation or switch of PPI therapy, (cessation defined as longer than 60 days not covered by a prescription.)

1. **Plan for addressing confounding**

Potentially confounding variables have been selected based on their possible association with the risk of TB, as listed in part K. These variables will be explored and potentially adjusted for in a multivariable Cox regression model. However, we believe substantial confounding is unlikely in this study as risk factors for TB are not expected to be associated with the choice of specific PPI, with the exception of calendar year. It is possible that rates of TB have changed over time and local prescribing guidance for preferred PPI has varied over the years mainly based on cost considerations. PPI preference could also be dictated by differential drug interactions between individual PPIs, as noted above for tacrolimus and ciclosporin and people with a history of taking either drug will be excluded.

1. **Plan for addressing missing data**

There is known missingness in the smoking and alcohol status and BMI variables. From previous experience of studies involving people taking long term medication such as PPIs it is expected that <10% of patients will have missing data. We plan to conduct a complete case analysis, which relies on the assumption that the probability of these data being missing is independent of TB risk, conditional on covariates5; given the small amount of missing data, any violation of the assumption is unlikely to importantly affect the results. Ethnicity is likely to have substantially more missing data. Again, we will conduct a complete case analysis with this variable included in the model, recognising the reduction in sample size will be greater and that this is a limitation of the study.

1. **Limitations of the study design, data sources and analytical methods**

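### The ciclosporin/tacrolimus exclusion is undated and does not reach patients who start either drug after entry, so part of the channelling it targets stays in the primary contrast (minor)

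*Protocol*

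**What the plan says.** Under Exposures, Outcomes and Covariates, the protocol says of ciclosporin and tacrolimus: "both immunosuppressive drugs, are known to interact with omeprazole but not other PPIs". It draws the consequence, "It is possible that people at higher risk of TB will therefore be given PPIs other than omeprazole", and for that reason "patients with a history of use of either drug will be excluded from the study population". The Plan for addressing confounding repeats the rule in similar words: "people with a history of taking either drug will be excluded".

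Under Data/ Statistical analysis, "follow up time will begin at the first prescription for lansoprazole or omeprazole/pantoprazole". Exposure is then time-varying. At a direct switch, "exposure will be updated to the new PPI from the date it is prescribed", and those who start on omeprazole or pantoprazole and later receive lansoprazole "will transition to the lansoprazole group at that time and vice versa".

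**The concern.** The protocol names a specific channelling mechanism and treats it as serious enough to exclude patients. The mechanism does not stop at cohort entry. A patient who starts tacrolimus while on omeprazole has the same reason to be moved to another PPI as one who was already taking it. If the move is to lansoprazole, higher-risk time enters the lansoprazole group.

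The missing date is a problem on either reading. If history means use before entry, later starters are not covered. If it means any use in the record, eligibility depends on events after follow-up has begun. The protocol does date the comparable TB exclusion under Study Population, to before the first PPI.

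At stake is modest confounding of the primary hazard ratio by a risk factor that the protocol itself identified and meant to remove.

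**Working it through.** The protocol gives no figure on this point, so there is none to reproduce. The check has four steps.

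**1. Rules side by side (all from the protocol).**

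| Rule | Treatment of ciclosporin/tacrolimus started after entry |
|---|---|
| Exclusion | Undated history of use; not reached on the plain reading |
| Exposure | Time-updated; switchers change group in both directions |
| End of follow-up (listed twice) | TB, death, transfer out, end of up-to-standard data; one list adds last data collection. Neither includes starting either drug |
| Covariates | Corticosteroids, chemotherapy, HIV, chronic kidney disease and rheumatoid arthritis are listed; neither drug is |
| Sensitivity analysis | Censors at cessation or switch of PPI |

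A patient who starts either drug after entry therefore stays in the primary analysis, unadjusted for it.

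**2. Illustrative size.** Let fL and fC be the shares of lansoprazole and comparator person-time in patients who started either drug after entry, and R their TB rate ratio. The observed hazard ratio is multiplied by

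B = (1 + fL(R − 1)) / (1 + fC(R − 1)).

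All three inputs are assumptions. The last column applies B to 0.80, the effect that Sample Size calls clinically relevant.

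| fL | fC | R | B | True 0.80 seen as |
|---|---|---|---|---|
| 0.1% | 0.05% | 10 | 1.0090/1.0045 = 1.004 | 0.804 |
| 0.2% | 0.05% | 20 | 1.0380/1.0095 = 1.028 | 0.823 |
| 0.4% | 0.05% | 20 | 1.0760/1.0095 = 1.066 | 0.853 |
| 0.2% | 0.1% | 10 | 1.0180/1.0090 = 1.009 | 0.807 |
| 0.2% | 0.1% | 20 | 1.0380/1.0190 = 1.019 | 0.815 |

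With fC held at 0.05%, fL from 0.1% to 0.4% and R from 10 to 20, B runs from 1.004 to 1.066, that is, about 1.00 to 1.07. A wider grid (fL 0.05% to 1%, R 3 to 20, fL two to five times fC) gives 1.0005 to 1.146. Its upper end needs 1% of lansoprazole time on these drugs: 1.19/1.038 = 1.146.

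**3. Against sampling error.** Take the 1:1 comparison of Table 1 with a true ratio of 0.80 and B = 1.028, so ln B = 0.0276.
- 1,200 exposed cases imply 1,200/0.8 = 1,500 comparator cases. The standard error is √(1/1,200 + 1/1,500) = 0.0387, and the shift is 0.71 of it.
- 200 exposed cases imply 250 comparator cases. The standard error is √(1/200 + 1/250) = 0.0949, and the shift is 0.29 of it.

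**4. Direction.** The formula treats exposure and TB as contemporaneous. The primary analysis does not: it moves TB dates 12 months earlier. TB recorded within 12 months after a switch from omeprazole to lansoprazole is then dated before the switch and counts as a comparator event, which lowers the hazard ratio. Only TB recorded later than that loads onto lansoprazole. The sensitivity analyses with shifts of 2 and 5 years widen this window; the one using recorded dates closes it.

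**The case against.** The strongest reply has four parts.

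- **The switch pathway is already handled.** The sensitivity analysis that censors at cessation or switch removes time after a move from omeprazole to lansoprazole. This stands, but only outside the primary analysis. That analysis also drops the later time of every switcher, so a changed result could not be traced to this cause. And lansoprazole users who start either drug have no interaction-driven reason to switch, so their time remains.
- **The effect is small and the inputs are invented.** This stands. The imbalance between groups is also unsupported: pantoprazole is in the comparator, so a move from omeprazole to pantoprazole changes no group. At a 2:1 split the factor is only 1.009 to 1.019 in the table above.
- **A statistical analysis plan would date the term.** That is possible for the date. But the protocol does fix the end-of-follow-up events and the covariates, and both omit these drugs.
- **Listed covariates act as proxies.** Chronic kidney disease, rheumatoid arthritis and corticosteroid use may capture part of the risk. The protocol does not say whether they are time-updated.

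Two stronger readings are tempting. A reader might infer that the bias runs in one direction only, or could carry the hazard ratio past 1. The 12-month shift defeats the first. On the second, a factor of 1.028 crosses 1 only if the true ratio already exceeds 1/1.028 = 0.973. A reader might also infer that this gap explains the protective association reported in the first amendment. The main pathway would hide protection, not create it, and nothing in the protocol shows that the opposing effect of the shift is large enough to matter.

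**Conclusion.** The gap is real: the safeguard stops at cohort entry, while the exposure it protects is updated throughout follow-up. It is of minor priority. Under the assumed inputs the hazard ratio is multiplied by about 1.00 to 1.07, which would show a true 0.80 as roughly 0.80 to 0.85. This rests on assumed person-time shares and TB rate ratios, on more such time under lansoprazole than under the comparator, and on a formula that ignores the TB date shift. The pull is mainly toward the null, but its sign is not established for the primary analysis. The case for acting is that the plan's own safeguard can be completed at almost no cost, not that the main result is in doubt.

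**What to change.** - Date the exclusion: ciclosporin or tacrolimus use recorded before the first PPI prescription.
- Censor follow-up at the first later prescription of either drug. Apply this to recorded dates, before TB dates and follow-up are moved earlier. If the order is reversed, TB recorded up to 12 months after the drug start could still be counted, credited to time before that start.
- If the primary analysis is to stay as it is, do this as a sensitivity analysis, or enter use of either drug as a time-updated covariate.
- Apply the same rule to the herpes zoster control analysis, since its confounders come from the same covariate list.

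The cost is one extra censoring date from prescription records, and probably little person-time. The first amendment says the TB analysis has already been run, so the change now means a re-run, which should be labelled as added after the result was known.
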